## Abstract

**Introduction:**

Acute psychological stress, as well as unusual experiences including
hallucinations and delusions, are common in critical care unit patients and have
been linked to post-critical care psychological morbidity such as post-traumatic
stress disorder (PTSD), depression and anxiety. Little high-quality research has
been conducted to evaluate psychological interventions that could alleviate
longer-term psychological morbidity in the critical care unit setting. Our
research team developed and piloted a nurse-led psychological intervention, aimed
at reducing patient-reported PTSD symptom severity and other adverse psychological
outcomes at 6 months, for evaluation in the POPPI trial.

**Methods and analysis:**

This is a multicentre, parallel group, cluster-randomised clinical trial with a
staggered roll-out of the intervention. The trial is being carried out at 24 (12
intervention, 12 control) NHS adult, general, critical care units in the UK and is
evaluating the clinical effectiveness and cost-effectiveness of a nurse-led
preventative psychological intervention in reducing patient-reported PTSD symptom
severity and other psychological morbidity at 6 months. All sites deliver
usual care for 5 months (baseline period). Intervention group sites are
then trained to carry out the POPPI intervention, and transition to delivering the
intervention for the rest of the recruitment period. Control group sites deliver
usual care for the duration of the recruitment period. The trial also includes a
process evaluation conducted independently of the trial team.

**Ethics and dissemination:**

This protocol was reviewed and approved by the National Research Ethics Service
South Central - Oxford B Research Ethics Committee (reference: 15/SC/0287). The
first patient was recruited in September 2015 and results will be disseminated in
2018. The results will be presented at national and international conferences and
published in peer reviewed medical journals.

**Trial registration number:**

ISRCTN53448131;
Pre-results.

Strengths and limitations of this studyPOPPI is the first, large, multicentre cluster-randomised clinical trial
evaluating a complex intervention commencing in the critical care unit and aimed
at reducing longer-term psychological morbidity for critical care survivors in the
UK.POPPI has strong patient and public involvement, with former critical care
patients involved in the development of the research question and intervention,
training of key trial staff and as members of oversight committees.The trial has an embedded economic evaluation and an independent process
evaluation.The primary outcome is patient-reported and it is anticipated that there may be
20%–25% missing data.

## Introduction

More than 170 000 patients are admitted to adult, general, critical care units in
the National Health Service (NHS) each year.^1^ It
has been estimated that approximately 50% of critically ill patients suffer serious
emotional distress, and up to two-thirds have unusual experiences such as hallucinations
and delusions, while in the unit.^2 3^ Emotional
distress, including severe symptoms of anxiety, low mood and panic, may be caused by a
range of stressful experiences that are common in the critical care unit: fear of dying;
invasive treatments such as mechanical ventilation; pain and discomfort; inability to
communicate; and terrifying hallucinatory delusions.^2 4–6^ The hallucinations and delusions of critical
care unit patients have been linked to delirium, the provision and withdrawal of
sedative and other psychoactive drugs, effects of illness (such as sepsis), immobility,
and sensory and sleep deprivation.^3 5 7^
Critical care unit hallucinations frequently have horrifying themes such as conspiracy
to kill by staff, torture, poisoning, demons, extortion or organ theft;^8^ thus a vicious cycle of stress, confusion and
terror is common for critical care unit patients.

Experiencing acute psychological stress in the critical care unit, or having frequent
memories of hallucinations and delusions, are among the identified risk factors for
longer-term post-critical care post-traumatic stress disorder (PTSD), depression,
anxiety or cognitive impairment.^5 9–13^ Systematic reviews of survivors of critical care identified high
rates of PTSD (median 20%)^4 14^ and depression
(median 30%),^15 16^ months or years after
leaving critical care. Patients who develop serious long-term psychological distress are
at much higher risk of further physical morbidities and mortality,^17–19^ representing a serious burden to patients, to
their carers and to NHS.^20 21^

Little high-quality research has been conducted to evaluate psychological interventions
that could alleviate the emotional distress experienced by patients in critical care,
with a view to preventing longer-term psychological morbidity.^22^ The introduction of valid psychological assessment tools for use
with critical care patients (eg, the intensive care psychological assessment tool
(IPAT))^23^ has made evaluation of psychological
interventions more feasible. Research informing the best timing to provide psychological
interventions suggests that postdischarge (eg, at 6 weeks^24^ or at outpatient follow-up clinics^21^) may be too late, and earlier intervention could be more beneficial.^25^ In today’s NHS, practitioner psychologists
are still a scarce resource, and a more pragmatic approach would be to standardise brief
evidence-based psychological interventions to be carried out by existing critical care
staff, who would be given the necessary training.

Our research team developed and piloted a nurse-led psychological intervention for
critical care unit patients which commences within the unit and is based on up-to-date
evidence concerning psychological techniques that are effective in: (A) reducing acute
emotional distress, (B) reducing the impact of unusual experiences such as
hallucinations and delusions and (C) preventing PTSD after a trauma. These are all
psychological problems commonly associated with admission to critical care. We
hypothesised that these existing evidence-based psychological interventions could be
modified to reduce the stress and trauma experienced by critical care unit patients, and
be delivered by specially trained, well-motivated critical care nurses. There is an
urgent need to evaluate their effectiveness in the critical care unit setting.

This protocol was informed by the Psychological Outcomes following a nurse-led
Preventative Psychological Intervention for critically ill patients (POPPI) feasibility
study (ISRCTN61088114) which looked at feasibility and acceptability of both the
intervention and the trial procedures.

## Methods

### Aim and objectives

The POPPI trial aims to evaluate the clinical effectiveness and
cost-effectiveness of a complex nurse-led preventative psychological intervention in
reducing patient-reported PTSD symptom severity, and other reported psychological
problems, at 6 months. The specific objectives are:to evaluate the effect of the complex intervention on patient-reported PTSD
symptom severity and other psychological outcomes and quality of life at
6 months; andto estimate, in an integrated economic analysis, the cost-effectiveness of
the intervention.

In addition, an integrated process evaluation will be conducted to assess the
fidelity, dose and reach of the implementation of the intervention, and to identify
important contextual factors to better understand how the intervention may work.

### Study design and setting

The POPPI trial is a multicentre, parallel group, cluster-randomised clinical trial
(cluster-RCT), conducted in 24 NHS adult, general, critical care units.

### Intervention

The POPPI trial will evaluate a intervention comprising three elements:Creating a therapeutic environment in critical careThree stress support sessions for patients screened as acutely stressedRelaxation and recovery programme for patients screened as acutely
stressed

An education package (two training courses and associated materials) to train
critical care staff to carry out the three elements has been developed and piloted by
our research team and will be described in detail elsewhere (paper under review for
publication).

### Sites

NHS adult, general, critical care units (‘sites’) are eligible to
participate if they are able to commit to the following criteria:show that recruitment, data collection and delivery of the intervention are
feasible;adherence to cluster-randomisation;Identify two joint-Principal Investigators (PIs) (a nurse and a
doctor) to lead the trial locally;agree, where possible, to recruit all eligible patients and to maintain a
screening and enrolment log; andcontinue active participation in the Case Mix Programme (CMP)—the
national clinical audit for adult critical care in England, Wales and
Northern Ireland coordinated by the Intensive Care National Audit &
Research Centre (ICNARC).

Sites who piloted the intervention during the POPPI feasibility study are not
eligible to participate in the trial.

#### Randomisation

The 24 sites will be randomly assigned to either the intervention group (n=12) or
the control group (n=12), by the ICNARC CTU, using a restricted randomisation
approach to ensure balance across the groups in terms of geographical location,
hospital teaching status and size of unit. For each group of eight sites, the
individual sites will be randomised (4:4) in their second month of recruitment. It
is necessary to randomise on a cluster (‘site’), rather than
individual level to avoid contamination of usual care, as it would not be possible
to restrict parts of the intervention to individual patients.

Sites randomised to the intervention group are responsible for selecting three
POPPI nurses based on a person specification which includes:Registered nurse with ≥3 years critical care clinical
experienceEffective communicator, with patients and their families, colleagues and
collaboratorsAble to work flexiblyInterested in improving psychological care of patientsOrganised and able to manage a busy schedule

#### Timeline

The 24 sites will open to recruitment in three groups of eight sites at 2-month
intervals and recruit patients over a 17-month period (see figure 1). Control group sites will deliver usual care for the
duration of the recruitment period. Intervention group sites will deliver usual
care from months 1 to 5. Usual care is defined as patients receiving
psychological support or treatment at the discretion of the treating clinician(s)
following standard practice at their site.

**Figure 1 F1:**
[figure not shown]
POPPI cluster-randomised clinical trial schedule.

After month 5, intervention group sites will undergo a 1-month transition period,
during which they will transition from delivering usual care to delivering the
intervention (see figure 2). At the beginning
of the transition period, all POPPI nurses at a site will attend a 3-day POPPI
nurse training course. Following the training course and completion of a local
intervention site initiation visit, the POPPI nurses and local education/research
teams will commence delivery of the POPPI intervention. During the transition
period, each POPPI nurse should deliver stress support sessions to at least one
recruited patient, identified (using the IPAT) as being stressed and at high risk
of psychological morbidity. In parallel, the POPPI nurses and local
education/research teams will encourage culture change in their unit to create a
therapeutic environment. This will be done by ensuring all clinical critical care
staff complete the POPPI online training and through other educational activities
(eg, seminars and short presentations, bedside teaching and display of materials
reinforcing key messages from the POPPI online training). At the end of this
transition period, the POPPI nurses will undergo a skills development assessment.
Following the transition period, the intervention will be delivered until the end
of the recruitment period.

**Figure 2 F2:**
[figure not shown]
Site timeline during transition period. IPAT, intensive care
psychological assessment tool.

#### POPPI nurse training course

The POPPI nurse training course is a 3-day central course to train POPPI nurses in
their new role. The focus of the course is on learning and practising the skills
required to deliver the stress support sessions with patients. The course was
designed by the trial team in consultation with experts in medical education and
cognitive behavioural therapy training, and is delivered by a psychologist, two
senior nurses and a research assistant.

The course will cover:Understanding critical care patients’ stress (including patient
representative talks and videos)Learning the skills needed to deliver stress support sessionsContent of each of the stress support sessionsObserving (in person and expert videos) example stress support
sessionsPractising each of the stress support sessionsUsing the patient booklet to create personal action plansDebriefing and support arrangements

Associated materials include: a precourse theory booklet, a training folder and
POPPI nurse training manual on the three stress support sessions; a tablet
computer with a ‘relax and recover’ app for patients to use with
help from nurses and family; and a self-help booklet and digital video disc (DVD)
for patients to take home.

The POPPI nurse role also includes; encouraging clinical staff in their units to
complete the POPPI online training; promoting the screening of patients with IPAT;
and teaching good communication skills and psychological care (reinforcing key
messages from the POPPI online training) at the bedside. These tasks will be
completed in conjunction with the research/education teams at each intervention
site as a team approach and training will be provided by the trial team at
intervention site initiation visits held locally.

#### Debriefing and support for POPPI nurses

All POPPI nurses will be allocated a trainer from the POPPI training team to
provide debriefing and support following the training course. Debriefing and
support will focus on enhancing nurses’ skills and discussing
patients’ cases. The first debriefing and support session will be carried
out once a POPPI nurse has delivered stress support sessions to their first
patient. Once all POPPI nurses at the site have delivered stress support sessions
to at least one patient each, the POPPI training team will visit the POPPI nurses
in their units to offer further support. During the visit, POPPI nurses will also
undergo a skills development assessment, to ensure they meet the required
standards for delivering the sessions. If necessary, further support and training
will be offered prior to the delivery of further sessions with patients. POPPI
nurses will continue to receive debriefing and support either via telephone call
or site visit.

#### Creating a therapeutic environment

Each intervention group site will create a therapeutic environment by encouraging
culture change in their unit. This will be facilitated by ensuring all clinical
critical care unit staff complete the POPPI online training and by teaching and
modelling good communication skills and psychological care at the bedside. The
POPPI online training is an online training course designed to aid the creation of
a calm, less stressful environment by reducing stressors in the environment and
using good communication with patients. The POPPI online training takes
approximately 30 min to complete and comprises five sections (understanding
the stresses of intensive care patients, reducing stress and fear in patients,
communicating with distressed patients, inspiring patients with confidence and
hope, and summary and assessment). Local research teams will enumerate all
clinical critical care staff at the start of the transition period, and then
monthly thereafter to ensure new staff members are registered for the POPPI online
training.

In addition, intervention group sites will ensure that POPPI materials are clearly
displayed (eg, posters) and distributed (eg, pocket cards) throughout the
unit.

### Patients

Patients admitted to participating units will be routinely screened against the
eligibility criteria:

#### Inclusion criteria

Age 18 years or greaterGreater than 48 hours in the critical care unitReceipt of level 3 critical care (for any period of time) during
first 48 hours in the critical care unitBetween +1 and −1 on the Richmond Agitation Sedation
Scale^26^Glasgow Coma Scale Score of 15English-speakingAbility to communicate orally

#### Exclusion criteria

Pre-existing chronic cognitive impairment, such as dementiaPre-existing psychotic illness, such as schizophreniaPre-existing chronic PTSDReceiving end-of-life carePreviously recruited to POPPI

Patients who meet the eligibility criteria in the unit will be approached and
provided with written and verbal information about POPPI by a member of the local
research team. Potential participants will be given the opportunity to ask
questions and time to discuss the trial with family or friends before making their
decision. After the person seeking consent is satisfied that the information has
been understood and questions have been answered, they will invite the potential
participant to sign the consent form. In providing informed consent, participants
are agreeing for the trial team to have access to their medical records for data
collection and to receive a follow-up questionnaire at 6 months. In
addition, participants recruited at intervention group sites from month
6 onwards (figure 1) will be offered
the option to provide consent to receive an assessment with IPAT and subsequent
stress support sessions (if applicable). Figure 3 shows the timeline for a patient recruited at an intervention group
site from month 6 onwards.

**Figure 3 F3:**
[figure not shown]
Patient timeline during the intervention
period. IPAT, intensive care psychological assessment
tool.

On entry into the study, the participant’s general practitioner (GP) will
be informed, by letter, of their recruitment into POPPI.

#### IPAT assessment

IPAT is a validated screening tool used to detect acute psychological stress and
unusual experiences such as hallucinations in critically ill patients.^23^ Consenting, eligible patients at
intervention group sites will be assessed using IPAT by a trained staff member as
soon as possible, but within 48 hours of consent being provided. A patient
is deemed highly stressed if they score seven or more on IPAT and should be
referred, as soon as possible, to a POPPI nurse to receive the three stress
support sessions. Patients who score less than 7 on IPAT will continue to receive
usual care as determined by the treating clinician(s). If the patient scores
5 or 6 on IPAT they will be reassessed daily, for a maximum of
3 days, until they either leave the critical care unit or the score drops
below 5.

#### Stress support sessions

The main objectives of the stress support sessions are for nurses to develop a
trusting relationship with patients, so patients can discuss concerns which they
might feel embarrassed or worried about communicating, and to reduce emotional
distress. There are three common components to each stress support session:
starting the session; building rapport; and finishing the session. In addition,
each session is structured as follows:Stress support session 1—‘helping patients understand and
cope with stress’Normalise reactionsEncourage communicationTeach coping strategiesStress support session 2—‘managing frightening thoughts
from critical care’Stress reactionsExplain stressful thinkingTeach ‘check out my fear’ techniqueStress support session 3—‘creating confidence and hope for
a good recovery’Summarise and reviewAction planFuture expectations

The three stress support sessions are to be delivered by the same POPPI nurse
ideally within 1 week, with the first stress support session starting as
soon as possible, but within 48 hours following IPAT assessment. Each
session lasts approximately 30 min and ideally (at least) the first session
is delivered in the critical care unit, but sessions can be delivered elsewhere in
the hospital if the patient moves. If a patient shows signs of distress or fatigue
during the session, then the session can be stopped and a new visit can be
arranged at a more appropriate time. The State-Trait Anxiety
Inventory (STAI)^27^ will be used
to assess a patient’s anxiety prior to session one (at baseline) and at the
end of stress support session 3. If a patient is showing serious signs of distress
at the end of their three sessions, their medical team will be informed.

#### Follow-up

All participants will be sent a follow-up questionnaire by the ICNARC CTU
6 months postrecruitment. The questionnaire contains the PTSD Symptom Scale
– Self-Report version (PSS-SR),^28^
the Hospital Anxiety and Depression Scale (HADS)^29^ the EuroQoL health questionnaire (EQ-5D-5L)^30^ and a health services and resource use questionnaire.
Questionnaire packs include a self-addressed stamped envelope and a pen for ease
of return. Non-responders will be telephoned 3 weeks later to check whether
they have received the questionnaire and, if preferable, they will be given the
option to complete the questionnaire over the telephone. If completed
questionnaires received at the ICNARC CTU indicate the presence of signs of
serious stress, anxiety or depression, a referral letter from DW (lead
clinical investigator) will be sent to the patient’s GP or the local PIs at
the recruiting site.

### Outcomes

#### Primary outcomes

The primary outcome for the clinical evaluation is patient-reported PTSD symptom
severity at 6 months, measured using PSS-SR,^28^ which conforms to the Diagnostic and Statistical Manual of Mental
Disorders (fourth edition) diagnostic criteria for PTSD and which has been
validated for use in critical care unit survivors.

The primary outcomes for the economic evaluation will be incremental costs,
quality-adjusted life years (QALYs) and net monetary benefit at
6 months.

#### Secondary outcomes

Secondary outcomes are:days alive and free from sedation to day 30;duration of critical care unit stay;PSS-SR greater than 18 points at 6 months;^31^anxiety and depression at 6 months, measured using HADS;^29^health-related quality of life (HRQoL) at 6 months, measured by
EQ-5D-5L^30^ andestimated lifetime cost-effectiveness.

### Data collection

Table 1 shows the patient data
collection schedule. The following data are collected by local research teams for all
patients while in hospital:Patient details (identifiers, sociodemographics)Clinical/baseline data (date/time of critical care unit admission and
consent, eligibility criteria, quality of life score, STAI^27^ score, prior delirium (assessed by
the Confusion Assessment Method for the Intensive Care Unit (CAM-ICU),^32^ documented pre-existing anxiety or
depression)Critical care unit stay data (duration of: delirium (assessed by CAM-ICU),
sedatives, anxiolytics, anaesthetics, sleep medications, antipsychotics,
analgesics, antidepressants, vasoactive agents and mechanical
ventilation)Hospital discharge data (discharge status, date of discharge/death)POPPI intervention data (for patients recruited at intervention group sites
during the intervention period—IPAT Scores, delivery of stress
support sessions, STAI Score after session 3)

**Table 1 T1:** Patient data collection schedule

	Baseline (at point of recruitment)	End of critical care unit stay	Intervention group sites—during transition and intervention periods			Six months postrecruitment
			Before SSS-I	During sessions	After SSS-III	
Collected inhospital						
Patient details	✓					
Clinical/baseline data	✓					
Critical care unit stay		✓				
IPAT assessment			✓			
SSS delivery				✓		
STAI	✓				✓	
Collected via follow-up questionnaires sent to patients						
PSS-SR						✓
HADS						✓
EQ-5D-5L						✓
Health service and resource use						✓

EQ-5D-5L, EuroQoL Health questionnaire; HADS, Hospital Anxiety and
Depression Scale; IPAT, Intensive care Psychological Assessment Tool;
PSS-SR, Post-traumatic Stress Disorder Symptom Scale - Self Report version;
SSS, stress support session(s); STAI, State-Trait Anxiety Inventory.

Follow-up data (PSS-SR, HADS, EQ-5D-5L, health services and resource use) are
collected via the patient follow-up questionnaire at 6 months postrecruitment.
In addition, data will be linked to CMP and will include demographics,
surgical status, acute severity of illness and duration of organ support, and
duration of critical care unit stay. Support for the collection and use of
patient-identifiable data has been approved for CMP by the Patient Information
Advisory Group (PIAG) under Section 251 of the NHS Act 2006—approval number:
PIAG 2-10(f)/2005. Survival at 6 months will be ascertained through NHS
Digital. All data are managed in accordance with ICNARC CTU standard operating
procedures.

The process evaluation will consider both quantitative and qualitative data.
Mixed-methods data will be collected for all three component parts of the
intervention, to elucidate the degree to which the intervention was delivered as
intended. Quantitative data will include the rate of online training uptake,
treatment fidelity of the stress support sessions, and routinely collected screening
and recruitment data. At intervention group sites, qualitative data will be collected
in the form of researcher observations, interviews with staff and structured field
notes. An independent researcher will observe and discuss the delivery of the
intervention with the POPPI nurses and wider critical care unit staff, exploring
clinician experiences including those relating to barriers and facilitators to the
delivery of the intervention. The process evaluation will also incorporate visits to
a purposively selected sample of control group sites. Qualitative data will be
collected to understand wider trial processes including strategies to ensure/promote
recruitment, and any changes in unit practice from baseline.

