#### Economic evaluation

A cost-effectiveness analysis (CEA) will be undertaken to assess the relative
cost-effectiveness of the intervention versus usual care. Resource use and outcome
data will be used to report cost-effectiveness at 6 months and to project
the lifetime cost-effectiveness of each strategy.

The cost analysis will take a health and personal health services perspective.
Resource use data will be combined with unit costs from the NHS Payment by Results
database and from local Trust Finance Departments, to report the total costs per
patient at 6 months for intervention versus usual care.^35 36^

HRQoL data from the EQ-5D-5L questionnaires at 6 months will be combined
with survival data using linear interpolation to report QALYs at 6 months.
CEA will follow the intention-to-treat principle and report the mean (95% CI)
incremental costs, QALYs and net monetary benefit at 6 months.

CEA will use multilevel linear regression models that allow for clustering^37^ including a random effect of site and a
fixed effect of period. The analysis will adjust for prespecified baseline
covariates at both patient level and site level.

Lifetime cost-effectiveness will be projected by encapsulating the relative
effects of the alternative strategies on long-term survival and HRQoL, combining
extrapolations from the patient survival data, with external evidence on long-term
survival and HRQoL.^38 39^ The long-term
survival of patients will be extrapolated from the cluster-RCT data by fitting
alternative parametrical survival curves (eg, Weibull, exponential, lognormal, log
logistic and Gompertz) to the observed survival data. The method of parametrical
extrapolation of survival for the base case will be chosen on the basis of model
fit and plausibility when compared with age-gender matched general population
survival.^40^ Survival will then be
extrapolated according to the chosen parametrical function for the duration
of years that parametrical curves predict excess mortality compared with
the age-gender matched general population, after which we will assume that
all-cause death rates were those of the age-gender matched general population. In
the base case, quality of life calculated at 6 months will be assumed to
apply to each subsequent year of life, after allowing for decrements in quality of
life according to advancing age. We will project lifetime costs by applying
morbidity costs estimated at 6 months over the period of excess mortality.

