## Trial status

This paper presents the protocol (V.2.2, 6 March 2017) for the first, large, multicentre
cluster-RCT evaluating a complex intervention commencing in the critical care unit and
aimed at reducing longer-term psychological morbidity for critical care survivors in the
UK. The full p rotocol (including amendments) is available on the NIHR website. 45 The first participant was recruited in September
2015. At the time of first manuscript submission, data collection for the trial was
ongoing and due to be complete in December 2017. The trial results will be disseminated
in 2018 through presentations at national and international conferences and publication
in peer reviewed medical journals.

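### The only post-discharge survival ascertainment described is at 6 months, yet lifetime survival is extrapolated from trial survival; the model should use all deaths up to the linkage date

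*Protocol article*

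**What the plan says.** Under Data collection, the article says: "Survival at 6 months will be ascertained through NHS" Digital. Hospital discharge data also record dates of death, but no other source of deaths after discharge is described.

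Under Economic evaluation, long-term "survival of patients will be extrapolated from the cluster-RCT data by fitting" several parametric families (Weibull, exponential, lognormal, "logistic and Gompertz) to the observed survival data"). No censoring date is attached to that fit. The same section makes three further choices:

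- The base-case curve is chosen on "fit and plausibility when compared with age-gender matched general population" survival.
- The chosen curve applies for as long as the curves predict excess mortality; general-population death rates apply after that.
- Morbidity costs run over the same period of excess mortality.

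The projection combines "extrapolations from the patient survival data, with external evidence on long-term" survival and quality of life, and sensitivity analyses are to vary the extrapolation approach.

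Three statements fix the calendar. The "first patient was recruited in September 2015 and results will be disseminated in" 2018 (Abstract, Ethics and dissemination). Sites open at 2-month "intervals and recruit patients over a 17-month period" (Timeline). Data collection was "ongoing and due to be complete in December 2017" (Trial status). Lifetime cost-effectiveness is listed among the secondary outcomes.

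**The concern.** A 6-month horizon suits the 6-month QALYs. It suits a lifetime projection poorly, because the fitted curves must answer questions about the hazard after 6 months: which form it follows, when it meets that of the general population, and therefore how long the extra costs last. Comparison with the general population can rule out implausible curves, but it cannot show when excess mortality ends in these patients.

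If the curves are fitted to survival cut at 6 months, the trial would give up later deaths that the same type of linkage could return without contacting patients. Lifetime life-years, QALYs and costs would then depend more than they need to on the choice of curve and on external data.

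**Working it through.** **1. Calendar.** The 17 months of recruitment can be rebuilt from the schedule, taking the planned intervention period as 5 months:

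- per site: 5 baseline + 1 transition + 5 intervention = 11 months;
- stagger of three groups at 2-month intervals: + 4 = 15;
- final extension in all sites (Power calculation): + 2 = 17, as stated.

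Counting September 2015 as month 0, the last recruitment month is month 16 (January 2017), the last 6-month follow-up is month 22 (July 2017), and December 2017 is month 27.

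| Linkage date (assumed) | Last patient | First patient |
|---|---|---|
| July 2017 | 22 − 16 = 6 months | 22 months |
| December 2017 | 27 − 16 = 11 months | 27 months |

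With even recruitment over site-months, mean follow-up to December 2017 is about 18 months, or 18/6 = 3 times the potential person-time of a 6-month cut. Neither linkage date is stated in the article, and no reporting lag is allowed for.

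**2. Deaths gained.** The article gives no mortality figure, so the following are assumptions: N = 1378 (the article's minimum recruitment), 6-month mortality d of 5-20%, and Weibull survival with shape k of 0.4-0.7.

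With t in months, F(t) = 1 − exp(−λt^k) and λ = −ln(1 − d)/6^k.

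Central case, d = 10% and k = 0.5:

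- λ = 0.1054/2.449 = 0.0430.
- Cut at 6 months: 1378 × 0.10 = 138 deaths.
- Follow-up spread evenly over 11-27 months: the mean of √t is (2/3)(27^1.5 − 11^1.5)/16 = 4.33, so F ≈ 1 − exp(−0.0430 × 4.33) = 0.170. That gives about 234 deaths, a ratio of about 1.7.
- Follow-up spread evenly over 6-22 months: the mean of √t is (2/3)(22^1.5 − 6^1.5)/16 = 3.69, so F ≈ 0.147. That gives about 202 deaths, a ratio of about 1.5.

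Across the assumed ranges, deaths to December 2017 are about 1.5 to 2.1 times those at 6 months. If the hazard were constant (k = 1), the ratio would reach about 2.9.

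**3. Precision gained.** Trials were simulated under the same assumptions. A Weibull curve was fitted by maximum likelihood, and mean survival over 20 years was read from it.

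- Central case: separate runs gave an SD of 0.72 to 0.86 years with a 6-month cut, and 0.48 to 0.51 years with 11-27 months. Paired within runs, 0.72 to 0.50 is a fall of 31% and 0.84 to 0.48 is a fall of 43%.
- Over the ranges, the information gain with 11-27 months was 2.3 to 5.3 times. Since 1 − 1/√2.3 = 34% and 1 − 1/√5.3 = 57%, a fair summary over all runs is a fall of roughly 30-50%.
- With 6-22 months the information gain was 1.6 to 4.1 times, a fall in SD of 21% to 51%.

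**4. Choice of curve.** Two curves through 10% dead at 6 months give very different 20-year means: 4.7 years (exponential) and 13.0 years (Weibull, shape 0.5). That contrast is not a fair measure. Under the central case, dated deaths within 6 months already reject the exponential: the likelihood-ratio statistic averaged about 86 on 1 df, with a minimum of 25. A closer comparison is lognormal against Weibull. Six-month data favoured the true Weibull in 73% of 60 runs, against 90% with the longer follow-up, and the fitted 20-year means differed by about 2 years (14.9 and 12.8).

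**The case against.** The strongest reply is that the article never says the lifetime model is cut at 6 months. The 6-month ascertainment serves the 6-month QALYs, and the lifetime paragraph refers to observed trial survival without a cut-off. The Analysis section is an overview that defers to a full analysis plan, and the full protocol is held elsewhere. This stands in part. A reader might infer that survival is ascertained only at 6 months and that later deaths will be thrown away; the document does not say so. It does say that the one linked ascertainment it describes has a 6-month horizon, and it describes no other source of later deaths for the curves.

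A reader might also infer that the projection rests on the early phase alone. It does not: external long-term evidence, a general-population plausibility check, a switch to general-population death rates and sensitivity analyses are all planned. These limit the damage from a short cut, but they do not replace later deaths in the trial's own patients. Sensitivity analyses display uncertainty; they do not reduce it.

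Nor do the data support saying that 6 months cannot separate the candidate curves. Some forms, the exponential among them, would be rejected; discrimination between closer forms is weaker, not absent.

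Finally, the precision figures concern pooled mean survival under one Weibull run for 20 years. They omit the planned switch to general-population rates and say nothing direct about incremental QALYs, costs or net benefit. That limit stands.

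**Conclusion.** The point holds as a matter of moderate weight. The article ties its only described post-discharge survival ascertainment to 6 months, then relies on trial survival to select a lifetime curve and to set the duration of excess mortality and its costs. If the cut is 6 months, follow-up of 6 to about 22 months, or about 11 to 27 months by December 2017, goes unused.

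The size depends on assumed mortality and curve shape and on an unstated linkage date. Under those assumptions, 11-27 months brings about 1.5 to 2.1 times the deaths and an SD of the simple 20-year projection lower by roughly 30-50%. In the central case, deaths go from about 138 to 235 and the SD from about 0.7-0.85 to about 0.5 years. The effect on the planned incremental estimate is not quantified.

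The primary clinical outcome and the 6-month economic outcomes are untouched; only the secondary lifetime cost-effectiveness outcome is affected.

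**What to change.** State the survival censoring date for the lifetime model. Define its data as all deaths up to the date of the NHS Digital linkage, with survivors censored at that date. Fit and select the parametric curves, and judge when excess mortality ends, on those data. Keep survival to 6 months for the 6-month QALYs.

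The cost is one line in the linkage request and the matching line in the economic analysis plan. A check is also needed that consent and data-sharing terms cover deaths after 6 months. No patient contact or extra visit is required. If those terms do not allow it, say so and report the 6-month cut as a limitation of the lifetime results.
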